#### Secondary outcomes

The study will include five measures of secondary outcomes: individual touch perception, which will be collected at baseline of the first randomized intervention, and blood pressure, heart rate, respiratory rate, and oxygen saturation, which will always be collected at baseline and during the 2 h of recovery at minutes 1, 3, 5, 7, 10, 20, 30, 40, 50, 60, 70, 80, 90, 100, 110, and 120. In addition, in I5 these variables will be collected 1 h prior to the application of the massage at minutes 1, 3, 5, 7, 10, 20, 30, 40, 50, and 60.► *Blood Pressure*○ Blood pressure will be verified by an indirect method using a stethoscope (Littmann, Saint Paul, MN, USA) and an aneroid sphygmomanometer (Welch Allyn – Tycos, Skaneateles Falls, NY, USA) fixed on the left arm of the volunteers. To avoid errors in determining blood pressure, these measurements will be performed by a single evaluator. The measurements will be performed according to the criteria established by the VII Brazilian Hypertension Guidelines [25]► *Heart rate*○ To verify the heart rate, a cardio frequency meter (Polar Electro Oy, Kempele, Finland – model V800) will be used [22]► *Respiratory rate*○ Respiratory rate measurements will be performed by counting the respiratory incursions for 1 min without the participant being aware of the process, so that the usual breathing characteristics are not modified [26]► *Oxygen saturation*○ Oxygen saturation will be verified by means of a pulse oximeter (Mindray PM-50 Pulse Oximeter, China). The pulse oximeter is a device that provides blood saturation readings by evaluating the absorption behavior of oxyhemoglobin and deoxyhemoglobin in relation to red and infrared light lengths [27]► *Questionnaire on individual touch perception*○ The *Touch Avoidance Questionnaire* [28] is a questionnaire composed of 37 questions that evaluate the experience of the touch received by another person. One question addresses how invasive the touch is from the unknown person and the other question addresses the touch experience by a professional whose profession requires the same touches, such as masseurs. The questionnaire contains 37 questions, and the questions offer the alternatives: “true” and “false” for scoring the touch experience; however, we will only use two adapted questions and the answers will be given on a linear scale equivalent to 10 cm, where 0 is without any discomfort and 10 is extremely uncomfortable

### Sample size

As described above the primary outcome will be the HRV. The sample size calculation was carried out based on the study of Arroyo-Morales et al. [15] in which the SDNN Index of the HRV was selected, since it is an index that expresses the behavior of the ANS in a global way. To establish the sample size, a mean effect of 26.9 and standard deviation of 38.8 were chosen. The level of significance for the sample size is 5%, the power test is 80%, two-tailed test, and 10% of the total value of *n* is added to statistically supply the analyses in the case of withdrawals during data collection. The value obtained for the sample size was 33 participants, adding the 10% gave a sample of 36 volunteers. However, there are other indices besides the SDNN Index within the HRV, and this situation generates an environment where the sample size could be underestimated. In the same sense, due to the new proposal presented by the study, there are no trials in the literature that have the same proposal dynamics, and thus, for safety we will add four volunteers to ensure the statistical analysis of all HRV indices, thus totaling a sample of 40 participants.

### Statistical analysis

For analysis of the data of the population profile, the descriptive statistical method will be used and the results presented as values of means, standard deviations, median, minimum and maximum numbers, and confidence interval. The normality of the data will be evaluated through the Shapiro-Wilk test.

The comparisons of cardiorespiratory parameters and HRV indices between interventions (I1, I2, I3, I4, and I5) and moments (rest (R1) vs recovery moments (R2–R12)), the data are analyzed from the prism of the covariance analysis (ANCOVA), which will be adjusted for the baseline value of the evaluated variable and generated estimated means after such adjustment (extracting the variance explained by the confounding variables). The Levene test will be used to prove the homogeneity of the variances at the created moments, and the Bonferroni post hoc test will be used for comparison. To guarantee homogeneity of data the variable can will be transformed into logarithm.

For analysis of the moments (rest vs recovery moments), repeated measures ANOVA with the Tukey post test for parametric distribution or Friedman test with Dunnett’s post test for non-parametric distribution will be used and the analysis of the different groups will be performed by means of one-way ANOVA with the Tukey post test or the Kruskal-Wallis test with Dunnett’s post test.

The level of significance will be *p* < 0.05 for all tests. The SPSS statistical program (version 13.0) (SPSS Inc., Chicago, IL, USA) will be used for the analyses. Data integrity will be monitored by regularly scrutinizing data files for omissions and errors. Participants will be given an anonymous study ID to protect confidentiality, and only study investigators will have access to the final trial data set.

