#### Primary outcome

HRV will be used as the primary outcome as it is an important overall marker of post-exercise recovery [16]. The HRV analysis will be performed from the series of RR intervals captured by the cardiofrequency meter Polar Electro Oy – model V800, and linear methods analyzed in the time domain and frequency domain, and Poincaré plot. All HRV indices will be obtained through the *software* Kubios HRV – version 2.0 [20].

For this analysis, the time series of RR intervals will initially be subjected to digital filtering using the *software* Kubios HRV – version 2.0, supplemented by manual filtering, to eliminate premature ectopic beats and artifacts, and only series with more than 95% of sinus beats will be included in the study [20]. Through visual analysis of the time series, the absence of ectopic artifacts or beats that can interfere in the HRV analysis will be observed.

During the recovery period, the evaluated moments will be: R1 (initial 5 min of rest before performing the interventions), R2 (initial 5 min of recovery), R3 (fifth to 10th minutes of recovery), R4 (10th to 15th minutes of recovery), R5 (20th to 25th minutes of recovery), R6 (30th to 35th minutes of recovery), R7 (40th to 45th minutes of recovery), R8 (50th to 55th minutes of recovery), R9 (60th to 65th minutes of recovery), R10 (70th to 75th minutes of recovery), R11 (90th to 95th minutes of recovery), and R12 (115th to 120th minutes of recovery). It is worth mentioning that 256 consecutive RR intervals will be obtained at these moments [21].

HRV indices in the time domain (rMSSD and SDNN), frequency domain (low-frequency spectral component (LF) and high-frequency spectral component (HF)), and the Poincaré plot (SD1 and SD2) will be evaluated [22].

In the time domain, the rMSSD Index corresponds to the square root of the square mean of the differences between the adjacent normal RR intervals in a time interval expressed in milliseconds and evaluates the behavior of the parasympathetic autonomic modulation [22], while the SDNN Index represents the standard deviation of all normal RR intervals recorded in a time interval, expressed in milliseconds, and is considered a measure of global variability, that is, it evaluates both sympathetic and parasympathetic modulation [22].

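### R1 is both the ANCOVA covariate and a moment compared with R2–R12, so the rest-versus-recovery test does not hold 5%; a second method then repeats the test, with Dunnett's named after rank tests

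*Protocol article*

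**What the plan says.** All references are to the protocol article.

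- **Primary outcome** defines the HRV windows. The first is "R1 (initial 5 min of rest before performing the interventions"; R2 to R12 are recovery windows. R1 is the only window before the intervention, so for HRV it is the baseline.
- **Statistical analysis, second paragraph**, compares cardiorespiratory parameters and HRV indices between the five interventions "and moments (rest (R1) vs recovery moments (R2–R12)), the data are analyzed from the prism of the covariance analysis (ANCOVA". The same ANCOVA is one "which will be adjusted for the baseline value of the evaluated variable and generated estimated means after such adjustment". Levene's test checks homogeneity of variance, a log transform is available, and "the Bonferroni post hoc test will be used for comparison".
- **Statistical analysis, third paragraph**, returns to the same comparison: "For analysis of the moments (rest vs recovery moments), repeated measures ANOVA with the Tukey post test for parametric distribution". When the data are not normal, the alternative named there is the "Friedman test with Dunnett’s post test for non-parametric distribution". Groups are also compared again, by one-way ANOVA with Tukey or Kruskal-Wallis with Dunnett's. Every test is at p < 0.05.

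**The concern.** A baseline may be a covariate for later values, or the reference level they are compared with. Used as both in one model, it is regressed on itself. At R1 the outcome is the covariate, so the slope there is exactly 1; at a recovery moment it is the within-person correlation, which is below 1. One common slope cannot fit both, and the residual spread at R1 differs from that elsewhere whatever the data.

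HRV is the primary outcome, and the aims include whether massage brings recovery forward or strengthens it. A rest-versus-recovery test that misses its nominal level bears on those aims. A second test of the same comparison by another method adds the chance of two different answers. The follow-up named for the rank tests compares means with a control and is not a rank procedure.

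**Working it through.** The plan states no figure for this point, so there is none to reproduce. It gives no correlations either; 0.3, 0.5 and 0.7 are **assumptions**.

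**Set-up.** One intervention, 12 moments, equal variance σ² and equal correlation ρ between moments, n participants, no true change. The contrast of a recovery moment with R1 is the plain difference of means, because the covariate cancels. Its true variance is 2σ²(1 − ρ)/n. Only the standard error (SE) is at issue.

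**Reading A: ANCOVA with independent errors, R1 a level and the covariate.**
- Common slope b = (1 + 11ρ)/12 = 0.358 / 0.542 / 0.725.
- Residual variance at R1 is σ²(1 − b)². At a recovery moment it is σ²[(1 − ρ²) + (b − ρ)²].
- Averaging over 12 levels gives MSE = σ²(11/12)(1 − ρ)[(1 + ρ) + (1 − ρ)/12].
- The model variance is 2·MSE/n, so model SE / true SE = √{(11/12)[(1 + ρ) + (1 − ρ)/12]}.

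**Reading A with R1 removed as a level.** For recovery against recovery, MSE = σ²(1 − ρ²), so the ratio is √(1 + ρ).

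**Reading B: repeated-measures GLM with R1 as covariate.** This amounts to regressing (recovery − R1) on centred R1. The residual variance is σ²(1 − ρ²), against a true 2σ²(1 − ρ), so the ratio is √[(1 + ρ)/2].

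Type I error is 2[1 − Φ(1.96 × ratio)].

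| ρ (assumed) | A: SE ratio | A: type I | A without R1: SE ratio | B: SE ratio | B: type I |
|---|---|---|---|---|---|
| 0.3 | 1.12 | 2.9% | 1.14 | 0.81 | 11.4% |
| 0.5 | 1.19 | 2.0% | 1.22 | 0.87 | 9.0% |
| 0.7 | 1.26 | 1.4% | 1.30 | 0.92 | 7.1% |

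Simulation (n = 36, 4,000 data sets per correlation) agrees: reading A 2.9 / 2.4 / 1.5%, reading B 11.7 / 9.0 / 6.8%, unadjusted paired test 5.1 / 5.5 / 4.8%.

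**Levene in the same homogeneous data.** On residuals of the model that includes R1 it rejects in 35 / 68 / 92% of data sets. On residuals with R1 removed it rejects in 5 / 3 / 2%, and on the raw values at each moment in 4 / 1 / 0.1%.

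**Can the two analyses disagree?** In a larger simulation (40 participants, 5 sessions, 12 moments, SD 38.8, 300 runs, reading A), ANCOVA and a paired test of the same contrast differed on significance in 3–4% of null runs. With assumed true shifts of 8, 12 and 16 units (participant and session variance shares 0.5 and 0.2), they differed in 14%, 18% and 11%. At 12 units the ANCOVA was significant in 49% of runs and the paired test in 68%.

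**Does removing R1 repair the intervention comparison?** No. In that null simulation the I4–I3 contrast rejected in 33–37% of runs with R1 kept as a level and 31–34% with it removed, because an ordinary ANCOVA ignores that each participant contributes many values in all five sessions. One-way ANOVA, which treats the cross-over arms as independent groups, rejected in 0–1.3%.

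**The case against.** The strongest objection is that the sizes depend on a model the article does not fully state, and this stands. The text does not say whether the ANCOVA has independent errors. Under reading A the SE is too large, under reading B too small. Nor is the reading A inflation the work of R1: without R1 as a level it is slightly larger (ratio 1.14–1.30 against 1.12–1.26). A reader might infer that the double use of R1 inflates the SE by a fixed amount; the article does not support that.

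Three other tempting inferences also go too far.
- *Levene will force a log transform.* Only if it is run on residuals of the model containing R1. The article refers to variances at the moments, which may mean the raw values, and there it does not over-reject.
- *The p-values will conflict.* They can, but need not.
- *The whole trial rests on return to baseline.* Under Study interventions, the I4 and I5 comparison carries the massage question, and R1 is a proper covariate for that.

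It is also fair that Dunnett's may be a slip for Dunn's, and that a condensed article may leave a precedence rule to a fuller plan. But the name appears twice, and R1's double role and the repeated analysis are stated methods, not omitted detail.

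**Conclusion.** The point holds. As written, R1 is both covariate and compared level, the common-slope assumption fails by construction, and the rest-versus-recovery test does not hold its 5% level under either natural fit: about 1–3% with independent errors, about 7–11% as a repeated-measures GLM. The direction is therefore not determined by the text. These figures assume correlations of 0.3 to 0.7, equal across moments, and no true change.

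The duplicate analysis can give a conflicting answer, and the article does not say which counts. Dunnett's test is wrong as named after rank tests. The intervention comparison has a separate and larger problem, the ignored within-participant structure, which taking R1 out of the outcome does not cure. This should be corrected before analysis; it does not call the design or data collection into question.

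**What to change.** 1. **Between interventions.** Take R2–R12 as outcome and R1 as covariate only, in one mixed model with participant and session-within-participant effects, period, and intervention-by-moment terms. Let it replace the ordinary ANCOVA and the one-way ANOVA or Kruskal-Wallis comparison.
2. **Rest versus recovery.** Use one within-intervention repeated-measures or mixed analysis, not adjusted for R1, with R1 as reference level and many-to-one adjusted comparisons. Delete the duplicate analysis.
3. **Rank tests, if kept.** Replace Dunnett's with Dunn's test or Holm-adjusted Wilcoxon signed-rank tests, in both places.

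The cost is rewording the Statistical analysis section. No further participants, measurements or visits are needed.

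### The parametric rest-versus-recovery analysis uses Tukey over all 66 pairs of moments, although the question asked is 11 comparisons with R1 and the non-parametric branch names Dunnett

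*Protocol article*

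**What the plan says.** The Primary outcome section defines 12 HRV moments. They run from "R1 (initial 5 min of rest before performing the interventions") through eleven recovery windows, the last being "and R12 (115th to 120th minutes of recovery").

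The Statistical analysis section states the comparison over time as "moments (rest (R1) vs recovery moments (R2–R12"). It then gives two branches for this question:

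- Parametric: "For analysis of the moments (rest vs recovery moments), repeated measures ANOVA with the Tukey post test for parametric distribution".
- Non-parametric: "Friedman test with Dunnett’s post test for non-parametric distribution".

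The same section also names an ANCOVA for interventions and moments, adjusted for the baseline value of the variable, after which "the Bonferroni post hoc test will be used for comparison". The threshold is common to everything: "The level of significance will be *p* < 0.05 for all tests".

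**The concern.** A comparison of each recovery moment with rest is a many-to-one question, and Dunnett's procedure is built for it. Tukey is built for all pairs and sets a higher bar for each comparison, because it also protects comparisons between recovery moments. The article gives no use for those.

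Two things are at stake:

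- **Sensitivity.** After the stress protocol, the trial needs to see whether HRV is still below its resting value at each moment. A stricter bar than the question requires means that real remaining deficits are declared significant less often.
- **Consistency.** The choice between branches follows the distribution of the data. Two HRV indices from the same men could be judged against different families of comparisons, one of 66 pairs and one of 11, only because one passed a normality test.

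**Working it through.** **Inputs from the article.** 12 moments, R1 to R12 (Primary outcome); 40 participants, effect 26.9 and SD 38.8 for SDNN (Sample size); α = 0.05 (Statistical analysis). The design assumptions are "The level of significance for the sample size is 5%, the power test is 80%, two-tailed test".

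**The plan's own figure.** n = 2 × [38.8 × (1.960 + 0.842) / 26.9]² = 32.7, rounded up to 33, as stated. Adding 10% gives 36.3, against the stated 36. This calculation is for a single unadjusted comparison. It reproduces 33 either as two independent groups, or as a paired comparison in which 38.8 is the SD of each measurement and the correlation is zero.

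**Counting the comparisons.** All pairs: 12 × 11 / 2 = 66. Pairs involving R1: 11. Pairs between recovery moments: 66 − 11 = 55.

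**Critical values.** Repeated measures ANOVA with 40 men and 12 moments has (40 − 1) × (12 − 1) = 429 error degrees of freedom. Equal correlations between moments are assumed.

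- Tukey: q(0.95; 12, 429) / √2 = 4.647 / 1.414 = 3.29, a per-comparison two-sided p of about 0.0011.
- Dunnett, 11 comparisons with one control, correlation 0.5: 2.755 by numerical integration, p about 0.0061. Simulation agrees to within 0.002.
- Bonferroni over the 11 contrasts: 2.85.
- Ratio of Tukey to Dunnett: 3.286 / 2.755 = 1.19.

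**Power.** Noncentral t with 429 degrees of freedom and noncentrality d × √40, where d is the remaining deficit in SDs of the within-person difference. The article does not give that SD, so a range is shown.

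| d | Tukey | Dunnett | Bonferroni over 11 |
|---|---|---|---|
| 0.3 | 8% | 20% | 17% |
| 0.4 | 23% | 41% | 37% |
| 0.5 | 45% | 66% | 62% |
| 0.6 | 69% | 85% | 83% |
| 0.8 | 96% | 99% | 99% |

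**At the protocol's own effect.** If 38.8 is the SD of each measurement with zero correlation, d = 26.9 / (38.8 × √2) = 0.49, and power is 43% with Tukey against 64% with Dunnett. If 38.8 is the SD of the difference, d = 26.9 / 38.8 = 0.69, and power is 86% against 95%.

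**Equivalent statements.** The deficit detectable with 80% power is 0.65 SD with Tukey and 0.57 SD with Dunnett. For equal power Tukey needs [(3.286 + 0.842) / (2.755 + 0.842)]² = 1.32 times as many participants.

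**Does the ANCOVA cover the same question?** Its sentence mentions the R1 comparison, but the model adjusts for the baseline value. R1 then enters as the covariate, and the adjusted means compare interventions and recovery moments with each other, not with rest. In the parametric case, the repeated measures ANOVA with Tukey is the analysis that tests each moment against R1.

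**The case against.** The best case for the plan is that nothing in it is invalid. Tukey controls the family-wise error, and its 66 pairs include all 11 that are wanted. On this view, choosing it costs efficiency but is not an error. Validity does stand, and it limits the finding to lost power and a mismatch with the question. It does not explain why the same question gets a different family in the other branch.

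A reader might infer that recovery will appear earlier in every session, by some number of minutes. The documents do not support that, for four reasons:

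- It needs recovery to be defined as the first moment not significantly different from R1. The article states no such rule. If that rule were used, it would be unsound with Dunnett or Holm too.
- It cannot apply to every session, because I1 and I2 contain no stress protocol and so have no exercise deficit to miss.
- Any figure in minutes rests on an assumed recovery curve. With an exponential decay and an assumed time constant of 30 min, the shift is 30 × ln(1.19), about 5 min. From R4 on, successive windows start 10 to 25 min apart.
- In simulations with an assumed starting deficit of 1.5 SD and time constants of 30 and 60 min, Tukey gave an earlier first non-significant moment than a cut-off of 2.84 in 34% and 41% of trials. In the rest the moment was the same.

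Two further points have been made. The main aim compares interventions with each other, and this point does not touch that comparison. That stands, and it keeps the severity moderate. It can also be said that a strict test over moments offsets the absence of a stated correction over six HRV indices. That does not stand: extra strictness over moments does not control error across indices, and it falls only on indices that pass the normality test.

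Finally, Dunnett is taken here as written. If an all-pairs rank procedure was meant after Friedman, the two branches would agree, but both would then be wider than the question.

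**Conclusion.** The point holds as a mismatch between question and method. The parametric branch adjusts for 55 comparisons that the article does not ask for, and the family changes with the normality result. The cost is power. The critical |t| is about 19% higher than needed, and the loss is 16 to 21 percentage points for remaining deficits of 0.4 to 0.6 SD, falling to about 3 points at 0.8 SD. At the protocol's own effect the loss is 9 or 21 points, depending on how the SD of 38.8 is read.

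Deficits from rest after the stress protocol will therefore be missed more often than necessary. The size rests on 40 complete participants, equal correlations between moments, and a within-person SD that the article does not give. The counts of 66, 11 and 55 rest on no assumption. No claim is made that the plan biases the comparison of interventions or that it misdates recovery. This is worth correcting before analysis but does not threaten the trial.

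**What to change.** In the parametric analysis of moments, replace Tukey with a many-to-one procedure against R1. Either of these would serve:

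- Dunnett with R1 as control, which matches the non-parametric branch as written.
- Holm over the 11 paired contrasts of R1 with each recovery moment. With each contrast's own SD, this does not need equal correlations. Its strictest step then uses 39 degrees of freedom and a critical |t| of 3.01, still below Tukey's 3.29.

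Leave the comparison of interventions as it is.

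The cost is one sentence of wording and no extra data or participants. What is given up is adjusted tests between recovery moments, which the trial does not ask for.

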**Methods:**

This is a randomized, cross-over clinical trial. Forty men aged 18 to 30 years, healthy and physically active according to the International Physical Activity Questionnaire will participate in the study. Participants will be randomized into groups, which will perform the five interventions of the study at randomized moments, one intervention per session: Intervention 1: control; Intervention 2: participants will receive the massage protocol; Intervention 3: performance of the stress protocol; Intervention 4: participants will perform the stress protocol and immediately after receive the massage; Intervention 5: participants will perform the stress protocol and 1 h after conclusion of the protocol will receive the massage. The sessions will occur with an interval of 1 week between them and, due to the technique used, blinding participants and therapists is not possible. The primary outcome measure is HRV that will be measured 2 h after the conclusion of each intervention, and secondary outcome measures, which include heart rate, respiratory rate, blood pressure, oxygen saturation, and individual touch perception, will be measured at specific moments in the course of each intervention.

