## Methods

### Study design

A randomized, cross-over, controlled clinical trial will be conducted at the Center for Studies and Care in Physiotherapy and Rehabilitation of the Universidade Estadual Paulista (FCT/UNESP), Presidente Prudente, São Paulo, Brazil. The study design is illustrated in Fig. 1. The study protocol follows the SPIRIT 2013 Checklist (Standard Protocol Items: Recommendations for International Trials) (Additional file 1) and TIDieR (Template for Intervention Description and Replication) so that the information and quality of the reports of the interventions are well described. The trial was registered at ClinicalTrials.gov (NCT03094676).

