### Randomization

Participants who meet the eligibility criteria and sign the consent form will be randomized, using simple randomization, for logistic reasons into five groups and the groups will be randomized into the different interventions of the study to determine the order of accomplishment. In order to guarantee the hidden allocation of the participants in the groups and the randomization of the study interventions, a researcher not involved in the recruitment will be responsible for this procedure using electronic software (Microsoft Office Excel). This researcher will be instructed not to previously inform the participants or other researchers about the procedures that will be performed in each session. The following figure presents the schematization of the aforementioned randomization processes (Fig. 2).

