### Design description

The study will be conducted in five interventions (Intervention 1 (I1); Intervention 2 (I2); Intervention 3 (I3); Intervention 4 (I4); Intervention 5 (I5)), and the groups will be randomized to perform these interventions at several moments, with a 1-week interval between interventions. Data collection will always be performed at the same period of day and in air-conditioned environments.

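### One-way ANOVA and Kruskal-Wallis are named for the different groups although every man performs all five interventions; used on I1–I5, they ignore the pairing and lose power

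*Protocol article*

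**What the plan says.** The Study design section declares the cross-over: "A randomized, cross-over, controlled clinical trial will be conducted". The abstract says of the randomised groups of participants: "which will perform the five interventions of the study at randomized moments, one intervention per session". Design description adds the spacing: "the groups will be randomized to perform these interventions at several moments, with a 1-week interval between interventions". Intervention is therefore a within-participant factor with five levels.

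In the Randomization section, groups are units that fix the order of sessions. Men are allocated "for logistic reasons into five groups and the groups will be randomized into the different interventions of the study to determine the order of accomplishment".

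Statistical analysis then describes three things:

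- An ANCOVA for comparisons between I1–I5 and between moments, "which will be adjusted for the baseline value of the evaluated variable and generated estimated means after such adjustment". No other model term is named. A variance check goes with it: "The Levene test will be used to prove the homogeneity of the variances at the created moments".
- Paired methods for time within a session: "For analysis of the moments (rest vs recovery moments), repeated measures ANOVA with the Tukey post test for parametric distribution or Friedman test".
- Unpaired methods for the groups, in the same sentence as the paired ones: "the analysis of the different groups will be performed by means of one-way ANOVA with the Tukey post test or the Kruskal-Wallis test".

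**The concern.** One-way ANOVA and Kruskal-Wallis treat their samples as coming from different people. Here the five samples come from the same men. The section uses paired methods for moments within a session and gives them up for comparisons across sessions, where the pairing is just as real.

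If the tests are applied to I1–I5, stable differences between men stay in the error term. The contrasts at risk are the ones the trial is run for: stress alone (I3) against massage straight after stress (I4) or one hour after it (I5), and I4 against I5. A difference missed for this reason could be read as evidence that the timing of massage does not matter. The article lists the cross-over design among its strengths, and these two tests would not use it.

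**Working it through.** **Inputs.** From Sample size: effect 26.9 and SD 38.8 (SDNN), two-sided 5%, power 80%, 33 men, 36 after adding 10%, 40 in total. From the design: five interventions per man. The correlation ρ between two sessions of the same man is not given, so 0.3, 0.5 and 0.7 are assumed.

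**Step 1: the plan's own figure.** For two independent groups, n per group = 2(z₀.₉₇₅ + z₀.₈₀)² × (SD/effect)² = 2 × (1.960 + 0.842)² × (38.8/26.9)² = 32.66, rounded up to 33. The stated 33 reproduces. Read as the SD of paired differences, 38.8 would give 16.3 (normal approximation). The article does not say which SD it is. The match with 33 supports taking 38.8 as the SD of a single session's value, as is done below.

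**Step 2: standard error of a pairwise difference, 40 men.**

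- Sessions treated as independent: 38.8 × √(2/40) = 8.68, whatever ρ is.
- Within participant: 38.8 × √(2(1 − ρ)/40).
- Ratio: 1/√(1 − ρ).

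**Step 3: type I error of the overall test at nominal 5%.** Simulation of 40 men × 5 sessions at one moment, with equal correlation between all sessions, no baseline adjustment and no dropout (10,000 runs for F and Tukey tests, 1,500 for rank tests).

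| ρ | SE, independent | SE, within | Ratio | One-way ANOVA | Kruskal-Wallis | Within-participant F |
|---|---|---|---|---|---|---|
| 0.3 | 8.68 | 7.26 | 1.20 | 1.0% | 1.1% | 5.0% |
| 0.5 | 8.68 | 6.13 | 1.41 | 0.15% | 0.13% | 5.1% |
| 0.7 | 8.68 | 4.75 | 1.83 | 0% | 0% | 5.2% |

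Friedman stays between 4.4% and 4.8% over the same range.

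**Step 4: power at the planned effect.** One intervention is shifted by 26.9, which is 26.9/38.8 = 0.69 SD.

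| ρ | Overall F, one-way | Overall F, within | Tukey I4–I3, one-way | Tukey I4–I3, within |
|---|---|---|---|---|
| 0 | 89.5% | 89.2% | 63.4% | 63.2% |
| 0.3 | 90.5% | 97.5% | 66.8% | 83.4% |
| 0.5 | 91.5% | 99.8% | 68.6% | 94.5% |
| 0.7 | 93.9% | 100% | 72.8% | 99.7% |

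Repeat runs put the one-way Tukey column at 66–74%. The row for ρ = 0 shows that part of the distance from 80% comes from the Tukey adjustment. The loss due to ignoring the pairing is the gap between the last two columns. At half the planned effect (13.45) the overall F tests also separate: 20% against 42%, 13% against 57%, and 6% against 81%.

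**Step 5: the ANCOVA, if fitted one moment at a time with session baseline but no participant term.** Over four assumed pairs of participant and session variance shares (0.3/0.2, 0.5/0.1, 0.5/0.2, 0.7/0.1):

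- Its reported SE was 7.51, 6.93, 6.20 and 5.19. The actual spread of its estimates was 7.13, 6.77, 5.92 and 4.81.
- With a participant term added, the SE was 6.95, 6.03, 5.63 and 4.49.
- Without the term the SE is therefore 8% to 16% larger (7.51/6.95 = 1.08; 5.19/4.49 = 1.16). The one-way tests carry an excess of 20% to 83%.

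**The case against.** The strongest reply is that the article assigns I1–I5 to the ANCOVA by name, and that elsewhere groups means the randomised order groups. The quoted sentence may then not be the intervention test at all. This stands as a point about wording, but it does not save the sentence. The order groups perform the same interventions in different sequences, so comparing them addresses none of the stated aims. On either reading the sentence has to change.

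A reader might infer more than the document supports, in four ways:

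- **That the whole between-intervention analysis discards the cross-over.** The missing participant and period terms in the ANCOVA are inferred from silence in a condensed article. The Levene check hints at a between-subject model but does not settle it. Step 5 shows that baseline adjustment recovers much of the loss.
- **That the trial risks spurious findings.** At a single moment the named tests err the other way, with intervals too wide and false positives below 5%. Inflation would arise if the 11 recovery moments entered as independent rows. Simulated without baseline, that gave a type I error of 17–72% for an assumed session variance share of 0.1 to 0.4. The article does not state such a model.
- **That power collapses at the planned effect.** The overall one-way F keeps 86–89% with 36 men and more with 40. The loss shows in the pairwise contrasts and at smaller effects.
- **That session trends bias the contrasts.** The order is randomised, and no figure in the document sizes a period effect.

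**Conclusion.** The point holds in limited form. One-way ANOVA and Kruskal-Wallis are unsuitable as written. They either ignore the pairing of five sessions in the same men or compare groups that carry no trial question. If used on I1–I5 at one moment, they inflate the pairwise standard error 1.20 to 1.83 times and hold Tukey pairwise power at the planned effect to roughly 66–74%, where a within-participant analysis reaches 83% to over 99%.

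These sizes rest on an assumed ρ of 0.3 to 0.7, equal correlation between sessions, 38.8 as the single-session SD, and all 40 men completing. The direction holds for any positive ρ; at ρ = 0 the two analyses agree. For the ANCOVA, the conclusion is only that its terms need to be stated: without a participant term it is mildly inefficient, and its standard errors are not those of the design. The sentence should be corrected before analysis, because as written it can govern every between-intervention comparison of the primary outcome.

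**What to change.** Replace the one-way ANOVA and Kruskal-Wallis, and specify the ANCOVA, as a single within-participant analysis for each HRV index:

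- A linear mixed model, or an ANCOVA with participant as a blocking factor. Fixed effects: intervention, moment, intervention-by-moment, period (session 1 to 5) and session baseline R1. Participant enters as the random or blocking factor.
- If moments are analysed together, add session within participant as a random effect, so that repeated moments are not counted as independent.
- Take I4–I3, I5–I3 and I4–I5 from this model, with the Bonferroni correction already planned.
- If data are skewed, use the log transformation that the section already allows. If a rank test is kept for interventions, use Friedman or Wilcoxon signed-rank.
- If a comparison of the order groups is really intended, say so and state its purpose.

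The cost is a revised statistical paragraph and some programming. No new data, visits or participants are needed.
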